### Eligibility criteria {10}

Hospitalized, or recently hospitalized, patients with liver cirrhosis with a pre-existing long-term PPI therapy will be screened. Patients with an evidence-based indication for PPI therapy, for example, recent diagnosis of severe reflux esophagitis (LA grade C or D) or peptic ulcers are excluded (for details see Table 1).

**Table 1 Tab1:** In- and exclusion criteria. Patients can be included in the trial, if they fulfil all the inclusion and none of the exclusion criteria

Inclusion criteria	Exclusion criteria
Male and female patients, at least 18 years old.	Diagnosis of reflux esophagitis LA grade C or D by EGD < 2 months prior to the screening visit without PPI therapy for at least 8 weeks prior to the screening visit.
Patients with liver cirrhosis. The diagnosis of liver cirrhosis may be based on (i) histology or (ii) a combination of clinical, laboratory and radiological criteria.	Peptic ulcers diagnosed by EGD < 28 days prior to the screening visit.
Hospitalization or recent hospitalization (0 to 42 days prior to the baseline visit) with complications of liver cirrhosis.	History of endoscopic therapy for oesophageal varices < 14 days prior to the screening visit.
Treatment with PPI for at least 28 days prior to screening.	Life-expectancy < 1 year (at the discretion of the investigator) due to extrahepatic malignancies, metastasized HCC, or other severe extrahepatic diseases (HCC without extrahepatic metastases or reduced life-expectancy < 1 year due to cirrhosis are not regarded as exclusion criteria).
Treatment with a PPI single standard dose/day or less for at least 7 days prior to screening.	Regular intake of NSAID on a daily basis (except for ASA 100 mg/day orally)
Females/males who agree to comply with the applicable contraceptive requirements.	One or more of the following measurements at the time of screening or documented up to 48 h before: ● Temperature > 38.5 °C ● Systolic blood pressure < 90 mmHg and heart rate > 100 bpm ● Catecholamine treatment > 0.1 μg/kg/min (terlipressin is allowed) ● Respiratory rate ≥ 22/min
Non-pregnant, non-lactating females.	Hypersensitivity or intolerance to esomeprazole, substituted benzimidazoles or other excipients of the IMP.
Ability to understand the patient information and to personally sign and date the informed consent to participate in the study, before completing any study-related procedures.	Ongoing therapy with nelfinavir.

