### Criteria for discontinuation or modifying allocated interventions {11b}

Patients who reach the safety endpoint (“evidence-based indication for re-therapy with PPI”; Table 2) will discontinue study medication. However, in case of clinically suspected peptic ulcer disease or signs of upper gastrointestinal haemorrhage rescue PPI treatment is permitted for up to 72 h or until an oesophago-gastro-duodenoscopy (EGD) is performed. If the EGD does not reveal a safety endpoint, rescue PPI therapy will be stopped and the patient continues study medication.

**Table 2 Tab2:** Primary, secondary and safety endpoints of the trial

Primary composite endpoint	Secondary endpoint
1.) Unplanned re-hospitalization	1.) Death
2.) Death	2.) Unplanned re-hospitalization
	3.) Any infection and differentiated by site of infection (SBP, pneumonia, urinary tract infection, blood stream infection, Clostridium difficile-associated enterocolitis, Norovirus infection, SARS-CoV-2 infection, others)
	4.) Acute hepatic decompensation and ACLF
	5.) Upper or lower gastrointestinal bleeding event
	**Safety endpoint:** Evidence based re-therapy with PPI due to the occurrence of any the following conditions:
	1.) Peptic ulcer diagnosed by EGD
	2.) Reflux esophagitis LA grade C or D diagnosed by EGD
	3.) Severe hemorrhagic gastritis diagnosed by EGD and histology
	4.) Mallory-Weiss syndrome diagnosed by EGD

*SBP* spontaneous bacterial peritonitis, *SARS-CoV-2* severe acute respiratory syndrome coronavirus 2, *ACLF* acute-on-chronic liver failure, *PPI* proton-pump inhibitors, *EGD* oesophago-gastro-duodenoscopy

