### Participant timeline {13}

Recruitment is planned to be completed within three years. With a trial duration 360 days per patient, time of first-patient-in to last-patient-out is four years. Figure 1 provides an overview of the trial design. After completion of the informed consent process, the screening visit will take place. Randomization will take place 0 to 14 days after screening during the baseline visit (visit 1, day 0). The study is split into two parts: “dose tapering phase” (days 1–14; tapering of the PPI dose in a blinded fashion, see above) and “main study phase” (days 15–360). Study visits and telephone interviews take place at the time-points indicated in Table 3. Study procedures during the respective visits and telephone interviews are summarized in Table 4.

**Table 3 Tab3:** Visits and time points

Screening visit	Up to 14 days before baseline
**Visit 1 (baseline)**	Day 0
**Visit 2**	Day 28 (± 2 days)
**Visit 3, 4, 5, 6**	Day 90, 180, 270, 360 (± 7 days, respectively)
**Telephone interview 1**	Day 14 (± 2 days)
**Telephone interview 2, 3**	Day 135, 225 (± 7 days, respectively)

**Table 4 Tab4:** Study procedures

Procedure	Screening	Baseline visit	Visits 2–6	Telephone interviews
Informed consent	X			
In-/exclusion criteria	X			
Randomization		X		
Medical history/demographics	X	X		
Adverse events/concomitant medication/endpoint assessment		X	X	X
Physical examination/height and weight		X	X	
Vital sign assessment	X	X	X	
Laboratory (haematology, biochemistry)		X	X	
Pregnancy test	X			
Stool samples & biobanking		X	X (visit 3)	
Ultrasound		X	X (visit 4, 6)	
Distribution and/or return of study medication and patients diaries		X	X	

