## Statistical methods

### Statistical methods for primary and secondary outcomes {20a}

The primary efficacy endpoint analysis will be performed according to the intention-to-treat (ITT) principle based on the full analysis set (FAS). The effects of continuation or discontinuation of PPI therapy with respect to the primary endpoint will be estimated and tested by Cox regression. The regression model will include treatment arm and categorized the severity of cirrhosis (MELD ≤ 13 vs. > 13) as fixed effects and the study centre as a random effect. As an estimated effect size, the hazard ratio (HR) between the two treatment arms will be given with the corresponding 95% confidence interval. The one-sided test of the superiority of discontinuation of PPI over the continuation of PPI at significance level 2.5% will be based on the corresponding asymptotic two-sided 95% confidence interval from the Cox regression model. The null hypothesis is rejected if the upper limit of the confidence interval is below 1.0. The analysis of the treatment effect with respect to the individual components of the composite endpoint and to secondary endpoints will be performed analogously with the (cause-specific) Cox model. Time to event outcomes will be visualized by Kaplan-Meier curves stratified by treatment group. Adverse event data will be summarized by the treatment group.

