Importantly, sudden PPI withdrawal in the intervention group may lead to clinically relevant overproduction of gastric acid with a recurrence of dyspeptic symptoms [53–55], which could lead to an increased risk for protocol violations (like the intake of PPIs or other acid-suppressive drugs). Therefore, PPI discontinuation will be achieved after dose tapering as previous data suggest a clinical benefit of dose tapering instead of abrupt withdrawal of PPI therapy [55].

In- and exclusion criteria are designed to ensure that the study population represents all patients with complicated liver cirrhosis in whom PPI discontinuation is feasible and may have positive effects on patients’ outcome: Especially hospitalized patients with complications of liver cirrhosis are at risk for re-hospitalization [20, 30, 56] and hospitalization itself is associated with increased mortality in this population [50]. Furthermore, the incidence of an infection (which is regarded a complication of cirrhosis in our protocol) is often a deteriorating event in the course of cirrhotic disease leading to ACLF [57]. As the study aims to evaluate the discontinuation of widely practiced “prophylactic” long-term PPI prescription without strong indication, a PPI therapy has to be documented for ≥ 28 days prior to screening. However, only patients taking a single PPI standard dose per day or less for at least 7 days are included in the trial, as patients receiving higher doses of PPI might be at an increased risk to suffer from gastric acid rebound symptoms [53–55] despite our PPI dose tapering protocol.

The exclusion criteria represent evidence-based indications for PPI therapy also in cirrhosis patients according to the German guidelines [58–60]. In these patients, discontinuation of PPI therapy might be harmful. Patients who underwent endoscopic therapy for oesophageal varices < 14 days prior to screening are also excluded, as PPI therapy may reduce the size of banding-ulcers after variceal band ligation [45, 46]. Patients with a life-expectancy below 1 year due to extrahepatic diseases or malignancies are excluded to avoid confounding of the primary efficacy endpoint, as these patients have a high risk to reach the primary endpoint independently from cirrhosis or the trial intervention. Also, patients who are regarded clinically unstable are excluded from the trial.

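### The secondary Cox models for infection and decompensation/ACLF omit the complication that brought the patient into the trial: a modest, cheaply recoverable loss of efficiency, not a bias

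*Protocol article*

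**What the plan says.** Table 1 (Eligibility criteria {10}) admits patients with "Hospitalization or recent hospitalization (0 to 42 days prior to the baseline visit) with complications of liver cirrhosis". The wording is plural and names no types.

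The Discussion links this criterion to prognosis: "the incidence of an infection (which is regarded a complication of cirrhosis in our protocol) is often a deteriorating event", with ACLF as the result.

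Table 2 lists as secondary endpoints "Any infection and differentiated by site of infection", acute hepatic decompensation and ACLF, and upper or lower gastrointestinal bleeding.

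Statistical methods {20a} sets out the primary model: "The regression model will include treatment arm and categorized the severity of cirrhosis (MELD ≤ 13 vs. > 13) as fixed effects", with centre as a random effect. For the other endpoints, the analysis of the composite's components and "to secondary endpoints will be performed analogously with the (cause-specific) Cox model". Randomization (Sequence generation {16a}) is stratified by centre and the same MELD split. The planned subgroups in {20b} do not include the index complication.

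**The concern.** Two of the secondary endpoints are, by the protocol's own account, the same kind of event as the index complication or a consequence of it. A patient recruited after an infection may well differ in later infection or ACLF risk from one recruited after, say, a bleed. The stated models carry no term for this, and MELD category need not capture it.

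In a Cox model, leaving out a prognostic baseline factor moves the estimated treatment HR towards 1 and lowers power. These endpoints matter to the trial's explanation. Sample size {14} bases the assumed benefit partly on fewer infectious complications, so a less efficient infection analysis weakens the link between the primary result and its proposed mechanism.

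**Working it through.** **The plan's own figure.** From 50% vs 65% at 6 months, HR = ln(0.50)/ln(0.35) = 0.660. Events at two-sided 5% and 80% power: Schoenfeld gives 182 (HR 0.66) or 183 (HR 0.6603), and Freedman gives 188. The stated 184 is reproduced within 3%. It concerns the primary endpoint only; the article states no power or event rate for any secondary endpoint.

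**Inputs from the article.** 476 patients, 1:1 (238 per arm); 360 days of follow-up; 20% loss.

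**Assumed inputs, not in the article.** Prevalence of the index factor 30%; 360-day control risk of the secondary endpoint 20% or 40%; treatment HR 0.66, borrowed from the primary endpoint; factor HR 2 or 3, with 5 as an extreme.

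**Simulation.** Exponential event times, exponential dropout reaching 20% at 360 days, 1,500 runs per scenario, Cox models with and without the factor, one-sided 2.5% rejection.

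| Control risk | Factor HR | Power without | Power with | Mean HR without | Mean HR with |
|---|---|---|---|---|---|
| 20% | 2 | 43.0% | 42.7% | 0.65 | 0.65 |
| 20% | 3 | 39.9% | 41.5% | 0.67 | 0.66 |
| 20% | 5 | 37.5% | 41.7% | 0.68 | 0.66 |
| 40% | 2 | 69.4% | 70.7% | 0.67 | 0.66 |
| 40% | 3 | 65.9% | 69.9% | 0.68 | 0.66 |
| 40% | 5 | 58.0% | 70.7% | 0.70 | 0.66 |

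Monte Carlo SE of a single power figure is at most about 1.3 points, e.g. sqrt(0.42 × 0.58/1500) = 0.013. The small negative difference in the first row is noise.

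**Cross-check.** Power ≈ Φ(0.5 × sqrt(events) × 0.4155 − 1.96), where 0.4155 = −ln 0.66. With 148 events (40% risk, factor HR 2) this is Φ(0.57) = 0.71, and with 72 events (20% risk) Φ(−0.20) = 0.42. Both match the adjusted models, so adjustment restores the power that the event count should deliver.

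**Does MELD already do the job?** A further simulation put a MELD term, correlated with the index factor, into both models (prevalence 30%, treatment HR 0.66, all assumed). The gain was about 1 to 3 points at factor HR 2 and 3 to 7 at factor HR 3, so including MELD does not remove it.

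**Validity.** With no treatment effect, one-sided rejection was 2.2% to 3.3% without the factor and 2.5% to 3.3% with it (nominal 2.5%, Monte Carlo SE about 0.4 points). Omission does not inflate type I error.

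**The case against.** The strongest defence is that the primary model contains exactly the stratification factors, a standard and coherent choice that contradicts nothing in the article. The word analogously may fix only the class of model and leave room for endpoint-specific covariates in the full protocol or SAP. No effect size for the index complication is given. The prognostic remark concerns infection and ACLF only, and nothing is said about an index bleed predicting later bleeding. Much of this stands: it rules out calling the omission an error, and it makes the bleeding term conditional. It does not remove the point, because the article states the model's terms, carries them over to the secondary endpoints, and itself supplies the reason for one further term.

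Three stronger readings are tempting and unsupported.

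- *Chance imbalance as bias.* At 30% prevalence the between-arm difference has SD sqrt(2 × 0.3 × 0.7/238) = 4.2 points, so a 95% range of about ±8.2 points. Under randomization this is random error that the confidence interval already allows for.
- *A strong, specific, already documented predictor.* The article gives no strength. A patient may have several complications. No coded field is shown; Table 4 lists only medical history, and that the type is on record is inferred from the eligibility check.
- *Index episodes counted as endpoints*, because Table 4 marks the baseline visit in the row "Adverse events/concomitant medication/endpoint assessment". That row combines three items, and a baseline mark is needed for concomitant medication alone. No passage says that an episode present at entry counts. An explicit onset rule is ordinary detail for the full protocol or SAP.

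**Conclusion.** The point holds as an efficiency improvement to a stated model. Under the assumptions above, adjusting for the index complication gains roughly 0 to 7 power points at factor HRs of 2 to 3. Without it, the mean HR moves from about 0.66 to at most 0.68. The gain is near zero if the factor is weak or events are few. It would reach 4 to 13 points only at a factor HR of 5, for which the article offers no support. Part of the HR difference reflects non-collapsibility: the two models estimate slightly different conditional effects, and neither is wrong. The primary endpoint, the 184 events and type I error are untouched. If the full protocol or SAP already names such a covariate, nothing remains to be done.

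**What to change.** In Statistical methods {20a}, after the sentence on secondary endpoints, pre-specify before unblinding:

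- an indicator for infection at the index hospitalization in the any-infection model and in the decompensation/ACLF model;
- an indicator for gastrointestinal bleeding at the index hospitalization in the bleeding model, if the number of events allows;
- no added term in site-specific infection models with few events (Table 2 has eight site categories).

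Take the indicators from the eligibility and medical-history records, with a coding rule that lets one patient have several index complications.

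The cost is one or two degrees of freedom per model and the work of coding consistently across 18 sites. Patient care, sample size and the primary analysis do not change. Do not extend the fix by starting a patient's time at risk when an index episode resolves: entry to the risk set would then depend on a post-randomization event that treatment could influence, which would weaken the randomized comparison.

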### Who will take informed consent {26a}

The principal investigator or a trained and designated physician has to obtain written informed consent from the patient prior to any study-related procedures. Patients will first have ample time to read the patient information. An investigator will provide the patients with information on the study. After the patient had ample time for consideration and formulation of questions (which could also mean that the patients first discuss the decision with friends or family members), and if all questions are answered the patient will be asked to personally sign the informed consent form. A copy or a second original of the signed informed consent form must be given to the patients for their records.

### Additional consent provisions for collection and use of participant data and biological specimens {26b}

Study participants have the option to consent on the collection of additional biobanking samples. Importantly, if the study participant does not provide informed consent for biobanking, the patient can still participate in the main study.

## Interventions

### Explanation for the choice of comparators {6b}

Patients in the intervention group discontinue a pre-existing long-term PPI therapy and replace it with placebo, while the pre-existing PPI treatment in the control group is replaced with esomeprazole 20 mg/day. Esomeprazole 20 mg was chosen as the comparator, because it is the only PPI which is assumed as “safe” for patients with advanced cirrhosis according to the available data on pharmacokinetics [48]. Moreover, 20 mg esomeprazole is equivalent to a PPI standard dose [49] and therefore adequately reflects the “common use” of PPI medication in clinical routine.

### Intervention description {11a}

All patients discontinue their previous PPI therapy during the baseline visit to start study medication on day 1 of the trial: Patients randomized to the intervention group receive placebo (P-Tablette weiß 7 mm Lichtenstein, Winthrop Arzneimittel GmbH, Frankfurt am Main, Germany) and patients randomized to the control group receive esomeprazole 20 mg/day (Nexium mups, Grünenthal GmbH, Aachen, Germany) over a period of 360 days. To prevent patients from gastric acid rebound symptoms caused by sudden PPI withdrawal, study participants will undergo a dose tapering phase over a period of 14 days in which they take the study medication from drug dispensers (“trial starter drug dispenser”; intervention group: placebo on days 1, 3, 5, 7, 9, 10, 12, and 13 and esomeprazole on days 2, 4, 6, 8, 11, and 14; control group: esomeprazole 20 mg days 1 to 14). After that, the patient will take the trial medication from “study medication packages” each containing 100 capsules placebo or esomeprazole 20 mg, respectively. Patients are provided with the “trial starter drug dispenser” and one “study medication package” during the baseline visit (visit 1). Furthermore, they receive a “study medication package” at visit 3 (day 90), 4 (day 180) and 5 (day 270).

### Criteria for discontinuation or modifying allocated interventions {11b}

Patients who reach the safety endpoint (“evidence-based indication for re-therapy with PPI”; Table 2) will discontinue study medication. However, in case of clinically suspected peptic ulcer disease or signs of upper gastrointestinal haemorrhage rescue PPI treatment is permitted for up to 72 h or until an oesophago-gastro-duodenoscopy (EGD) is performed. If the EGD does not reveal a safety endpoint, rescue PPI therapy will be stopped and the patient continues study medication.

**Table 2 Tab2:** Primary, secondary and safety endpoints of the trial

Primary composite endpoint	Secondary endpoint
1.) Unplanned re-hospitalization	1.) Death
2.) Death	2.) Unplanned re-hospitalization
	3.) Any infection and differentiated by site of infection (SBP, pneumonia, urinary tract infection, blood stream infection, Clostridium difficile-associated enterocolitis, Norovirus infection, SARS-CoV-2 infection, others)
	4.) Acute hepatic decompensation and ACLF
	5.) Upper or lower gastrointestinal bleeding event
	**Safety endpoint:** Evidence based re-therapy with PPI due to the occurrence of any the following conditions:
	1.) Peptic ulcer diagnosed by EGD
	2.) Reflux esophagitis LA grade C or D diagnosed by EGD
	3.) Severe hemorrhagic gastritis diagnosed by EGD and histology
	4.) Mallory-Weiss syndrome diagnosed by EGD

*SBP* spontaneous bacterial peritonitis, *SARS-CoV-2* severe acute respiratory syndrome coronavirus 2, *ACLF* acute-on-chronic liver failure, *PPI* proton-pump inhibitors, *EGD* oesophago-gastro-duodenoscopy

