**Methods:**

The STOPPIT-trial is a prospective, multicentre, randomized, double-blinded, placebo-controlled, parallel-group trial. In total, 476 patients with complicated liver cirrhosis who already receive long-term PPI therapy without evidence-based indication are 1:1 randomized to receive either esomeprazole 20 mg (control group) or placebo (intervention group) for 360 days. Patients with an indication for PPI therapy (such as a recent diagnosis of peptic ulcers, severe reflux esophagitis, severe hemorrhagic gastritis, recent endoscopic therapy for oesophageal varices) are excluded. The primary composite endpoint is the time-to re-hospitalization and/or death. Secondary endpoints include rates of re-hospitalization, mortality, occurrence of infections, hepatic decompensation and acute-on-chronic liver failure. The safety endpoint is defined as manifestation of an evidence-based indication for PPI re-therapy. The impact of PPI continuation or discontinuation on the intestinal microbiota will be studied. The recruitment will take place at 18 study sites throughout Germany. Recruitment has started in April 2021.

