### Relevant concomitant care permitted or prohibited during the trial {11d}

Open-label PPIs, h2-receptor antagonists and nelfinavir are prohibited during this trial (exception: rescue PPI therapy for up to 72 h in patients with suspected upper gastrointestinal bleeding events or peptic ulcers). Non-steroidal anti-inflammatory drugs (other than acetylsalicylic acid up to 100 mg/day) for more than 7 days during a period of 28 days are not permitted. Treatment with sucralfat for dyspepsia or symptomatic reflux disease is permitted.

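### Recent endoscopic therapy for varices is a PPI indication at entry but not on study, so a placebo patient treated endoscopically during the trial stays off PPI in a state the protocol excludes

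*Protocol article*

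**What the plan says.** **At entry.** The abstract (Methods) lists "recent endoscopic therapy for oesophageal varices" as an example of an indication for PPI that leads to exclusion. Table 1 in Eligibility criteria {10} sets the limit: "History of endoscopic therapy for oesophageal varices < 14 days prior to the screening visit". The Discussion says of the exclusion list as a whole: "The exclusion criteria represent evidence-based indications for PPI therapy also in cirrhosis patients according to the German guidelines", and continues: "In these patients, discontinuation of PPI therapy might be harmful". It then gives the reason for this particular criterion: "Patients who underwent endoscopic therapy for oesophageal varices < 14 days prior to screening are also excluded, as PPI therapy may reduce the size" of banding ulcers. Background and rationale {6a} refers to the same effect for PPI courses of up to 10 days after ligation.

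**On study.** Table 2 defines the safety endpoint, evidence-based re-therapy with PPI, by four diagnoses: peptic ulcer, LA grade C or D oesophagitis, severe haemorrhagic gastritis and Mallory-Weiss syndrome. Variceal endoscopic therapy and banding ulcer are not listed. Section {11b} allows rescue PPI for suspected ulcer or upper gastrointestinal bleeding, for up to 72 hours or until endoscopy, and then states: "If the EGD does not reveal a safety endpoint, rescue PPI therapy will be stopped and the patient continues study medication". Section {11d} adds: "Open-label PPIs, h2-receptor antagonists and nelfinavir are prohibited during this trial", with the 72-hour rescue as the only exception. Under Outcomes {12}, patients who reach the safety endpoint are censored at that time.

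**The concern.** The same clinical state has two statuses. Before randomization it is a reason not to withdraw PPI. After randomization it neither ends study medication nor permits PPI beyond a short rescue. The reason given at entry, the effect of PPI on banding ulcers, is not tied to the time of enrolment and would apply equally to a procedure on day 100. The article gives no reason for the difference.

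Two things are at stake. The first is safety: some placebo patients are kept off PPI in circumstances where the Discussion says withdrawal might be harmful. The second is interpretation: the trial sets out to study PPI use without an evidence-based indication, and for a short time these patients have what the abstract calls an indication. On-study procedures are foreseeable, because the population has been hospitalized with complications of cirrhosis and the Discussion describes an increased risk of variceal bleeding.

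**Working it through.** The point rests on comparing rules. The only arithmetic concerns how long the conflict lasts and whether the event target is affected.

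**1. Rules side by side**

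| | At entry | On study |
|---|---|---|
| Status of variceal endoscopic therapy | Named as a PPI indication (abstract); excluded if under 14 days before screening (Table 1) | Not among the four Table 2 conditions |
| PPI afterwards | Patient not enrolled, so not withdrawn | Rescue stopped, study drug continued ({11b}); open-label PPI barred ({11d}) |

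**2. Following the rules for a placebo patient**

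- *Treated for a bleed.* Rescue PPI may start on suspicion. Endoscopy shows varices, which are treated, and none of the four conditions. Rescue stops and placebo resumes. Even if {11d} is read as allowing the full 72 hours (3 days), at least 10 − 3 = 7 days of the course length cited in {6a}, or 14 − 3 = 11 days of the Table 1 window, pass without PPI.
- *Treated electively.* There is no suspected bleed or ulcer, so the rescue exception does not apply and the whole window passes without PPI.
- *Limits.* Controls remain on esomeprazole 20 mg, so only the placebo arm is without PPI. During days 1–14 the tapering schedule in {11a} still gives this arm esomeprazole on 6 of 14 days, so the conflict applies in full from day 15.

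**3. Which endpoints are reached**

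Objectives {7} counts only the first event, an unplanned admission or a death. An admission for variceal bleeding would usually be that event, so it precedes the procedure and nothing later changes it. Deaths and bleeds after it still count as secondary endpoints, because Outcomes {12} continues study drug and follow-up. The primary endpoint is reached chiefly when treatment is elective and the patient is still event-free. Sample size {14} assumes 50% of the withdrawal arm have had an event by 6 months. With a constant hazard, 0.50² = 25% would be event-free at 12 months, so this group shrinks over follow-up.

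**4. Event target**

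- HR = ln(0.50)/ln(0.35) = 0.660, matching the stated 0.66.
- Schoenfeld: D = 4(1.960 + 0.842)²/(ln HR)² gives 182 at HR 0.66 and 183 at 0.6603. Freedman gives 188. The stated 184 is reproduced; at 184 events the Schoenfeld power is 80.5%.
- 12-month risks with constant hazards: 1 − 0.35² = 87.75% and 1 − 0.50² = 75%, mean 81.375%. Expected events, with the planned 20% loss contributing none: 476 × 0.80 × 0.81375 ≈ 310.
- If Table 2 were changed and a further 5%, 10%, 20% or 30% of patients (assumed range) were censored without any event, about 294, 279, 248 or 217 events would remain. All exceed 184.

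**The case against.** The strongest reply is that an entry exclusion and a safety endpoint do different jobs. Reaching the safety endpoint stops study drug and leads to censoring. The article describes the benefit after ligation as short-lived, so keeping a transient state off that list is defensible, and the two lists need not match. This stands as far as it goes. But the list is not the only obstacle: {11d} separately bars any PPI outside the rescue, and no reason for the different treatment is given.

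The Discussion can also be read as setting variceal therapy apart from the guideline indications, since it says these patients are also excluded and claims only that PPI may reduce ulcer size. That is fair, but the abstract plainly calls it an indication, so the article would still disagree with itself. A banding ulcer might be recorded as a peptic ulcer. The text does not say so, and the entry criterion is the procedure, not a later ulcer.

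The article condenses a fuller protocol that is not shown, and a post-procedure instruction might be there. However, {11b} and {11d} state a rule and name its exception; they are not silent.

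Several stronger conclusions are tempting and are not supported:

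- A reader might infer that every later ulcer bleed, admission or death counts against discontinuation in the primary analysis. After a bleeding admission the first event has usually already occurred.
- A reader might infer that a short PPI course removes patients from the per-protocol set. The article names that set without defining it, and the primary analysis is by intention to treat.
- A reader might infer that variceal therapy is itself a reason to stop PPI. Rescue stops because no listed condition was found.

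Both arms follow the same blinded rule, so the randomized comparison remains valid.

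**Conclusion.** The inconsistency is real and lies in stated rules. Variceal endoscopic therapy is an indication and an exclusion at entry, and on study it has no status that permits PPI beyond a brief rescue. The conflict is confined to the post-procedure window and to the placebo arm. Its weight falls on patient safety, on the secondary endpoints of death and gastrointestinal bleeding, and on the claim that the trial concerns patients without an indication. It reaches the primary endpoint mainly through elective procedures in event-free patients.

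The size is unknown. A reader might assume that 10% to 30% of patients are treated on study, which is 238 × 0.10 ≈ 24 to 238 × 0.30 ≈ 71 per arm. The article supports no such rate, and the count would mix elective with emergency procedures and patients before and after their first event. The conclusion does not depend on it. The 184-event target reproduces and is not threatened.

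**What to change.** Reconcile the abstract, Table 1, Table 2, {11b}, {11d} and the Discussion so that variceal endoscopic therapy has a consistent status at entry and on study, or give the reason for the difference. Which rule applies is for the sponsor's clinicians to decide.

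Whichever is chosen:

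- state it explicitly in {11b} and {11d};
- record the date of each on-study variceal endoscopic therapy, so that it can be linked to the concomitant medication already collected (Table 4) and to the bleeding source already planned ({7});
- keep these patients in intention-to-treat follow-up;
- if Table 2 changes, state what follows for the censoring rule in Outcomes {12} and for the independent-censoring assumption in {20c}.

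The cost is a protocol amendment and one eCRF field, with no extra visits or procedures. Depending on the sponsor's choice, some placebo patients might have brief PPI exposure, which would slightly reduce the contrast between the arms.
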